### Blinding

This trial was designed as a pragmatic, randomized, controlled, triple-blinded trial with three parallel arms. All patients, surgeons, clinical investigators who are responsible for data collection, and statisticians will be kept unaware of group assignments until the final data analyses were completed. Although patients will be kept blind to their prescription, the computer-generated randomization table will be provided to the hospital pharmacy. Therefore, our hospital pharmacy will not be blinded to the randomization and will prepare all medications with a single packet of medicine as scheduled. Considering the success of blinding is a fundamental issue in clinical trials, blinding will be further verified with the Bang’s Blinding Index [49]. After the intervention, patients will answer a separate question (“Guess Duloxetine”, “Guess Placebo”, “Don’t Know”) in the blind assessor questionnaire, which attempts to measure the effectiveness of blinding.

### Perioperative care

All TKAs will be performed by the same orthopedic surgeon using the same approach. The routine perioperative analgesic strategy, including preemptive analgesia (celecoxib), intraoperative periarticular cocktail injection, postoperative patient-controlled analgesia (PCA) and celecoxib, and discharge medication (celecoxib). In case of patients suffering unbearable postoperative pain, morphine or other opioids will also be given, the opioid consumption would also be recorded and compared. In the duloxetine group, patients will receive a half-dose of preemptive duloxetine (30 mg/day) for a week before surgery, and a full-dose of duloxetine (60 mg/day) for six weeks after surgery. The maintenance dose (60 mg/day) of duloxetine was chosen based on previous publications [32, 43, 44, 50]. While patients in the placebo group and blank control group will receive placebo for the same period. All enrolled patients will receive the same standard preoperative publicizing and education, intraoperative type of anesthesia, postoperative care, and rehabilitation.

### Follow‐up period

During hospitalization, the basic metabolic panel will be obtained once or more to monitor serum sodium level, as hyponatremia is a duloxetine-induced complication that may occur early on after duloxetine initiation. In our routine clinical practice, patients are advised to return to the outpatient clinic for follow-up evaluation at one, three, and six months after surgery and subsequently every one year after surgery. Thus, in this clinical trial, all of the patients will be followed up at one, three, and six months after surgery. If patients are unwilling or unable to return to the study center for evaluation, they will be interviewed via telephone. Both the hospital and outpatient follow-up evaluation will be conducted by an investigator who is blinded to the experimental groups.

### Criteria for withdrawal

Participants will be informed that they are under no obligation to participate and have the right to withdraw consent for participation in this clinical trial at any point without prejudice, and their routine clinical care and follow-up will not be affected by declining to participate or withdrawing from the trial. Meanwhile, the investigator or regulatory authority can discontinue a patient’s participation in the clinical trial at any time if medically or otherwise necessary. Of note, it is not recommended to discontinue duloxetine abruptly, especially when taking the maintenance dose of 60 mg/day. Therefore, the participant who wishes to discontinue or withdraw must contact the investigator to obtain discontinuation advice.

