**Methods:**

This randomized controlled trial includes patients with knee osteoarthritis on a waiting list for primary unilateral TKA. Patients with preoperative CS will be randomly allocated to the perioperative duloxetine treatment group (duloxetine group) or the care-as-usual control group (placebo group). Patients in the duloxetine group will receive a half-dose of preemptive duloxetine (30 mg/day) for a week before surgery and a full-dose of duloxetine (60 mg/day) for six weeks after surgery. The primary outcome is the intensity of residual pain at six months after TKA, including the visual analogue scale, 11-point numeric rating scale, the sensory dimension of the brief pain inventory, and the pain subscale of the Knee injury and Osteoarthritis Outcome Score. The secondary outcome measures will include the pain and function related outcomes. All of the patients will be followed up at one, three, and six months after surgery. All adverse events will be recorded and immediately reported to the primary investigator and ethics committee to decide if the patient needs to drop out from the trial.

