### Randomization and allocation

After applying the selection criteria, the potentially eligible patients will be screened with the Central Sensitization Inventory (CSI) preoperatively, with a CSI score ≥ 40 indicating CS and a CSI score of < 40 indicating normal [46–48]. Patients with preoperative CS will be randomly allocated (1:1) to the duloxetine group or the placebo group by a computer-generated randomization list. After randomization, there will be a baseline assessment, such as patient demographics and baseline values for outcome measures. In addition, a group of patients who are assessed as normal will receive the placebo (as the blank control group). The hospital pharmacy will prepare indistinguishable capsules containing either duloxetine or placebo for the study. Randomization and allocation will be revealed only after the required number of subjects has been recruited and the data analysis has been completed.

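### As the article states it, duloxetine ends at 60 mg/day after six weeks with no step-down, against its own advice on stopping, and the advice route names only patients who wish to stop or withdraw

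*Protocol article*

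**What the plan says.** The regimen appears twice, in the Abstract (Methods) and under Perioperative care, and the two accounts agree. There is a one-week lead-in at 30 mg/day before surgery, followed by "a full-dose of duloxetine (60 mg/day) for six weeks after surgery". For the comparators, "patients in the placebo group and blank control group will receive placebo for the same period". Neither place gives a dose after week six, and no taper is mentioned elsewhere in the article.

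Criteria for withdrawal contains the precaution: "it is not recommended to discontinue duloxetine abruptly, especially when taking the maintenance dose of 60 mg/day". The action drawn from it is that "the participant who wishes to discontinue or withdraw must contact the investigator to obtain discontinuation advice".

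On contacts after surgery, Follow-up period states that "all of the patients will be followed up at one, three, and six months after surgery", with a telephone interview for those who cannot or will not attend. Adverse events provides for recording and treating events that patients report spontaneously or staff observe.

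**The concern.** The article describes the way up in dose and duration but not the way down. It then warns against a sudden stop and singles out the dose at which its own schedule ends. The safeguard attached to that warning is addressed to people leaving early. A patient who takes every capsule as planned neither wishes to discontinue nor withdraws, so the text does not reach that patient.

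What is at stake is the welfare of duloxetine-group completers, who should be the majority of that group. Safety is also one of the trial's stated aims, and effects of stopping would arise at a time when no assessment is scheduled.

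**Working it through.** The article gives no figure of its own to reproduce here. The check compares its statements and then places the last dose on the visit calendar.

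**Dose sequence as written (Perioperative care)**

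- Week before surgery: 30 mg/day for 7 days.
- After surgery: 60 mg/day for 6 × 7 = 42 days.
- After that: no dose stated, so a single drop from 60 to 0 mg/day.

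Criteria for withdrawal advises against an abrupt stop, especially from 60 mg/day. For a completer, the stated schedule and the stated precaution cannot both be followed.

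**Who is affected (Sample size)**

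- Planned in the duloxetine group: 50, which is the ceiling.
- Allowance for violators or dropouts: 20 %, so 50 × (1 − 0.20) = 40.
- Working range: about 40 to 50. The lower end is approximate, because a protocol violator may still finish the medication.
- Placebo and blank control groups: none, since they take placebo throughout.

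**Timing (Follow-up period)**

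Assume that one, three and six months fall at about days 30, 90 and 180.

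| Interval | Calculation | Days |
|---|---|---|
| One-month contact to last dose | 42 − 30 | 12 |
| Last dose to three-month contact | 90 − 42 | 48 |
| Last dose to six-month primary outcome | 180 − 42 | 138 |

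The one-month contact therefore comes while patients are still on treatment. The next one is nearly seven weeks after the last dose.

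**What a step-down would change**

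Assume 7 to 14 days at 30 mg/day. The article gives no length, so this range is for illustration.

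- Present course: 7 + 42 = 49 dosing days; 7 × 30 + 42 × 60 = 210 + 2,520 = 2,730 mg per patient.
- Added days: 7/49 = 14 % to 14/49 = 29 %.
- Added drug: 7 × 30 = 210 mg to 14 × 30 = 420 mg; 210/2,730 = 8 % to 420/2,730 = 15 %.
- End of dosing: day 42 + 7 = 49 to day 42 + 14 = 56.
- Gap to the primary outcome: 180 − 56 = 124 to 180 − 49 = 131 days.

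**The case against.** The strongest reply is that a journal article condenses a fuller protocol. How capsules are stepped down could sit in that protocol, in pharmacy instructions or in patient information. The precaution itself shows that the investigators know of the risk, which makes a plan for completers plausible. This stands as a limit: the article does not show that no taper exists, and a reader who inferred that the trial has none would go too far. It does not remove the point. The article gives the regimen by dose and duration, including the lead-in, states the precaution, and names who is to seek advice. Taken together, those statements leave completers stopping in the way it advises against.

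A second reply is that a section on withdrawal naturally speaks to those who leave, and that it does not forbid advice to others. That is fair, but no other section extends the advice to completers.

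A third is that patients are not out of reach. This is correct. It would be wrong to infer that there is no contact at which stopping could be discussed: the one-month visit or telephone interview comes about 12 days before the last dose. However, the article does not assign it that task, and advice alone cannot produce a step-down when patients hold only the blinded capsules packed for them.

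A fourth is that Adverse events already covers symptoms after stopping. It would record and treat those that come to notice, but it would not prevent them.

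**Conclusion.** The point holds for the regimen as stated. About 40 to 50 duloxetine-group completers would stop abruptly from 60 mg/day at about day 42, contrary to the article's own precaution, with no visit at or shortly after that day. The range rests on the planned group size and the 20 % allowance; the day count rests on six weeks of 42 days and on visits near their nominal dates.

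Two stronger conclusions are not supported. The first is that a known number of patients would be harmed: the article gives no frequency or severity for effects of stopping, so only exposure can be counted. The second is that the efficacy result is compromised: the primary outcome comes about 138 days after the last dose, and nothing here changes the sample size or the primary analysis. This is a patient-safety correction that should be made, with medium confidence because the full protocol is not at hand.

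**What to change.** - Under Perioperative care, add a short blinded step-down after week six. The 30 mg/day dose already used before surgery is an obvious candidate; the clinical leads should set the length.
- Give matching placebo capsules for the same days in the placebo and blank control groups, so that the schedule does not reveal allocation.
- Under Criteria for withdrawal, extend the precaution to the planned end of treatment.
- Give the stopping instructions at the one-month contact, in the same words for every group. No extra visit is needed.
- If the full protocol already contains a taper, one sentence under Perioperative care stating it is enough.

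The cost is a protocol amendment with ethics notification, updated patient information and more packing. The supply route exists, since "The hospital pharmacy will prepare indistinguishable capsules containing either duloxetine or placebo for the study". Under the assumed one to two weeks, each patient takes capsules for 7 to 14 more days, and duloxetine patients receive the additional 210 to 420 mg. Packing grows by 100 × 7 = 700 to 100 × 14 = 1,400 patient-days for the two randomised groups, or 150 × 7 = 1,050 to 150 × 14 = 2,100 if the blank control group also has 50 patients.

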### Outcome measurement

The following outcome parameters and patient characteristics will be retrieved from electronic hospital information systems or medical records, physical examination, and patient questionnaires.

### Primary outcome measures

The primary outcome is the intensity of residual pain at six months after TKA. The perception of residual pain will be measured with the visual analogue scale (VAS), 11-point numeric rating scale (NRS), the sensory dimension of the Brief Pain Inventory (BPI), and the pain subscale of the Knee injury and Osteoarthritis Outcome Score (KOOS) at six months after surgery [51–54]. These questionnaires have been proven to be valid and reliable, and the results of these questionnaires will help to ascertain the robustness of our results. The key postoperative time point of six months was chosen as this is recognized as the first possible time point to evaluate the ‘success’ of TKA in clinical practice.

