### Sample size

Sample size calculation was performed with the VAS score as the primary outcome measure. Based on the previous study, the smallest change score for the VAS score to be considered clinically relevant is 2 points (on a 0–10 scale) between the duloxetine group and the placebo group [32]. The power calculation is performed based on the VAS score difference using a two-sided hypothesis test at an alpha level of 0.05 and a power of 80 %, and a total of 38 participants is needed in each group [57–59]. Taking into account the possibility of 20 % violators or dropouts, we will include 50 patients in each group.

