### Statistical analysis

Analyses will be performed using the IBM SPSS software (version 21.0, IBM Corp., New York, NY, USA). All outcomes measures will be assessed using both the ITT (intention-to-treat, all randomly assigned patients) and PP (per-protocol, patients who completed the trial without any protocol deviations) data sets. The missing value will be imputed by the last-observation-carried-forward (LOCF) method. For continuous variables and descriptive values, means ± standard deviations (SDs) will be reported. For the enumerative variables, frequency and corresponding percentage will be calculated. For the variables with a normal distribution, statistical comparisons between the groups will be made by using a *t*-test. For variables with a non-normal distribution or ordinal level, the statistical comparison will be made using the Mann-Whitney U test. Outcomes with a discrete distribution will be expressed as percentages and analyzed by the *chi*-squared test or Fisher’s exact test as appropriate. A *P* value < 0.05 is considered statistically significant.

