## Discussion

Residual pain is the most common reason for patient dissatisfaction following TKA. Recently, several studies suggested that CS is associated with chronic postoperative pain and decreased satisfaction after TKA. Duloxetine has been used in an off-label way to treat centrally mediated chronic pain in patients with preoperative CS, but the efficacy of pain control after TKA remains unclear. Currently, the available evidence is extremely limited; thus, we designed this clinical trial to examine the efficacy and safety of duloxetine for postoperative pain after TKA in CS patients. The present study was designed based on previous literature, thus, our trial has some advances and strengthens when compared with previous similar RCTs [32]. First of all, except the duloxetine group and placebo group, we set an extra blank control group, which consists of normal patients without medication. Parents in the blank control group will provide the standard baseline for the trial, which will help to evaluate the magnitude of improvement. Second, several parameters will be included to measure the intensity of residual pain, including the VAS score, NRS score, BPI score, and KOOS score. The consistency of these parameters will help to ascertain the robustness of the results. Third, based on previous RCTs, we will collect all of the efficacy and safety related parameters, which will contribute to a more comprehensive evaluation of duloxetine.

We will ensure that this study is a genuinely randomized, controlled, triple-blinded trial through the full implementation of randomization, blindness, and concealment. We will conduct and report this clinical trial in strict accordance with the Consolidated Standards of Reporting Trials (CONSORT) [60]. It is important to acknowledge that the results of this trial will provide scientific and rigorous clinical evidence for the application of perioperative duloxetine in CS patients being scheduled for TKA.

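### Four pain scales share the primary outcome with none in the lead, but the sample size treats the VAS alone as primary, so the stated 5% error and 80% power describe only a single VAS test

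*Protocol article*

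**What the plan says.** The article describes its primary outcome in two ways.

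- **Four scales.** Under Primary outcome measures: "The perception of residual pain will be measured with the visual analogue scale (VAS), 11-point numeric rating scale (NRS"), followed by "the sensory dimension of the Brief Pain Inventory (BPI), and the pain subscale of the Knee injury and Osteoarthritis Outcome Score (KOOS) at six months". The abstract agrees: "The primary outcome is the intensity of residual pain at six months after TKA, including the visual analogue scale, 11-point numeric rating scale", and then the other two scales.
- **One scale.** Under Sample size: "Sample size calculation was performed with the VAS score as the primary outcome measure". The target is a VAS difference: "the smallest change score for the VAS score to be considered clinically relevant is 2 points (on a 0–10 scale"). With two-sided alpha 0.05 and 80% power, this gives 38 per group, raised to 50 for 20% violators or dropouts.

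Under Statistical analysis, "All outcomes measures will be assessed using both the ITT" and the PP data set, and a P "value < 0.05 is considered statistically significant". No scale and no analysis set is singled out there.

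The reason given for using several scales is robustness. The Discussion says: "The consistency of these parameters will help to ascertain the robustness of the results". The Secondary outcome measures section then lists the same four instruments again as measures of pain severity.

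**The concern.** A reader cannot tell from the article which result decides whether duloxetine worked. If the VAS is null and the NRS is significant, or three scales agree and one does not, the text supports more than one conclusion. Error rate and power are properties of a decision rule. The article states both for a VAS comparison but defines the primary outcome more widely. What is at stake is the trial's confirmatory claim: whether a reported success carries a 5% false-positive risk, and whether the trial has 80% power for the outcome it calls primary.

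**Working it through.** **Inputs from the article:** four primary scales; difference 2 points on a 0–10 VAS; two-sided alpha 0.05; power 80%; 38 evaluable and 50 enrolled per group; 20% loss; 1:1 allocation.

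**Inputs assumed:** the SD (not stated) and the correlation r between the test statistics of the four scales (not stated). Values of r = 0.5, 0.7 and 0.9 are shown. Each scale is given the same standardised effect as the VAS.

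**Step 1. The plan's own figure.** n per group = 2 × [(1.960 + 0.842) × SD / 2]². Without an SD, 38 cannot be reproduced from the stated inputs. Solving for the SD gives 2 / [√(2/38) × 2.802] = 3.11, a standardised difference of 2/3.11 = 0.643. At that SD, 38 per group gives 80% power for one VAS test at 0.05. For dropout, 38/0.8 = 47.5, so 48; the stated 50 covers this. The 38 and 50 are therefore coherent for a single VAS comparison.

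**Step 2. Rule A: any one of four scales at 0.05.** With independent tests, error = 1 − 0.95⁴ = 18.5%. That is an upper reference only, since four pain scales in the same patients will be correlated. The correlated cases come from simulating four equicorrelated z-statistics (1,000,000 draws), with mean 0 for error and mean 1.960 + 0.842 = 2.802 for power at 38 per group.

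| r | Error, any of four | Power, any of four |
|---|---|---|
| 0.5 | 15.6% | 97% |
| 0.7 | 13.0% | 94% |
| 0.9 | 9.4% | 88% |

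**Step 3. Rule B: all four scales at 0.05.** Error cannot exceed 5%, because a false claim needs at least one true null hypothesis to be rejected at 0.05. With all four nulls true it is 0.1%, 0.6% and 1.9% at r = 0.5, 0.7 and 0.9. For 50 per group, the mean is 2.802 × √(50/38) = 3.214, which gives single-test power of 90%.

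| r | Power, all four, n = 38 | Power, all four, n = 50 |
|---|---|---|
| 0.5 | 56% | 73% |
| 0.7 | 62% | 77% |
| 0.9 | 70% | 83% |

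The n = 50 column assumes that every enrolled patient contributes and that dropouts and carried-forward values do not dilute the effect.

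**Step 4. Two analysis sets.** Suppose a PP result could also establish efficacy, with PP an 80% subset and the ITT and PP tests correlated √0.8 = 0.89. Error for one scale would then be 7.1%. For any of four scales it would be about 21%, 18% and 13% at r = 0.5, 0.7 and 0.9.

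**The case against.** The strongest reply is that the article already leads with the VAS. The Sample size section calls it the primary outcome measure in the singular, and both the outcomes section and the Discussion present the set of scales as a check on robustness. Multiplicity rules and the choice of decisive analysis set are also often left to an analysis plan, which is not shown.

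Part of this stands. The lack of a rule for split results would not be a finding by itself. But the two descriptions of the primary outcome conflict within this document, and the robustness wording covers all four scales equally: it neither puts the VAS first nor makes the other three supportive. An unseen analysis plan could add a hierarchy, but the article's own sections would still disagree.

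Two stronger readings are tempting and are not supported.

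- A reader might infer that the trial may claim success on whichever of eight analyses (four scales in two sets) reaches 0.05. The article adopts no such rule. Reporting both ITT and PP is ordinary, nothing says that PP can carry the conclusion, and the stress on consistency points away from picking one scale.
- A reader might infer that error and power both fail. They fail under opposite rules: any-of-four inflates error while power rises, and all-of-four controls error while power falls. With all 50 per group contributing undiluted and r = 0.9, even the all-four rule reaches 80%.

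**Conclusion.** The point holds as an inconsistency that affects what the trial can conclude. The 5% and 80% apply to a single VAS test. At the stated 38 evaluable per group and the correlations examined, neither unadjusted rule over the four scales delivers both figures: any-of-four gives about 9–16% error, and all-of-four gives about 56–70% power. With 50 per group contributing undiluted, all-of-four power is about 73–83%, so the shortfall there is smaller and disappears at the highest correlation. The 13–21% error from also accepting a PP win is conditional on a rule that the article does not state.

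These sizes rest on assumed correlations of 0.5 to 0.9, an equal standardised effect on every scale, and the SD of about 3.11 implied by 38 per group. The inconsistency itself rests on none of them.

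**What to change.** Before unblinding, state in the same words in the abstract, Primary outcome measures, Sample size and Statistical analysis that the single primary analysis is the VAS at six months, duloxetine versus placebo, in the ITT set, two-sided at 0.05. Make the NRS, BPI sensory dimension and KOOS pain supportive outcomes and PP a sensitivity analysis, and say that none of these can establish efficacy by itself. The VAS is the natural lead because the sample size was computed on it; leading with another scale would reopen the mismatch with that calculation.

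The cost is a wording amendment, plus alignment of the registry entry (not seen here) if it differs. The 38 evaluable and 50 enrolled per group stay as they are, and no data collection changes. Because the article keeps allocation concealed until the analysis is complete, the choice can be made blind if it is made before then. The only loss is the option to claim success on another scale or analysis set.
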